**Fig. 2 Fig2:**
[figure not shown]
Overview of the RICH trial procedure

The investigators will prescribe the study drug. Both the participants and investigators will be blinded to the identity of the drug (TJ-43 or placebo).

Patients in both arms will also receive conventional antiemetic therapy, i.e., palonosetron (0.75 mg on day 1 administered intravenously), dexamethasone (9.9 mg on day 1 administered intravenously, 8 mg on days 2–4 administered per os), and aprepitant (125 mg on day 1 and 80 mg on days 2–3 administered per os), in accordance with established guidelines [5].

### Randomization and blinding

The participants will be assigned to either the TJ-43 group or the placebo group in a 1:1 ratio using a block randomization method. A randomization list has been pregenerated, and this assignment list will be kept in a safe until unblinding. The randomization list will not be disclosed to the investigators. The placebo drug is indistinguishable from TJ-43 in appearance. Therefore, both the investigators and participants will be blinded to the treatment group throughout the study. Unblinding will take place only after the trial is finished and data are fixed, except in the case of emergencies.

### Prohibited drugs

The concomitant intake of other *Kampo* medicines or other medicaments comprising a component of TJ-43 is prohibited during the administration of TJ-43 or placebo to avoid interactions or effects on the evaluation of drug efficacy.

### Criteria for discontinuing the protocol treatment

The following will be considered criteria for discontinuing the protocol treatment:Consent is withdrawnInvestigators judge that it is difficult to continue the test because of deterioration of the patient’s primary diseaseInvestigators judge that it is difficult to continue the test because of adverse eventsInvestigators judge that it is difficult to continue the test because of the development of severe diseases other than lung cancerThe patient is deemed ineligible for the trial after registrationThe patient’s medication compliance is inadequate and does not improve despite medication instruction after registrationThe patient discontinues the medication at their own discretionThe patient fails to visit the hospital after the trial has begunInvestigators judge that it is suitable to discontinue the test

### Data collection

After registration and assignment to treatments, prospective data will be collected for all patients, including sex, date of birth, physical findings, and clinical information (such as medical history, complications, and regimen of lung cancer chemotherapy). The investigators will measure the patients’ dietary intake during each meal from day 0 (the day before the start of chemotherapy) to day 7. For each meal, the weight of food (including tableware) before and after the meal will be measured. Dietary intake will be calculated by subtracting the weight of food consumed (including tableware) after the meal from that of food (including tableware) before the meal. The investigators will also check meals other than hospital diets.

In addition, the investigators will check changes in the patients’ QOL assessment at days 0, 7, and 22 or 29 (the start date of the next chemotherapy course), the incidence of any adverse events except anorexia, the proportion of patients who received dose-reduced cisplatin-including chemotherapy in the next course, the proportion of patients who delayed the start of cisplatin-including chemotherapy in the next course, and the proportion of patients requiring extended hospitalization.

Blood samples will be routinely collected at days 1, 7, and 22 or 29. Two sets of specimens will be drawn: routine monitoring samples and trial samples. Possible side effects, such as neutropenia and renal dysfunction, will be checked in both groups. The routine blood samples will undergo measurements of the hemoglobin concentration; leukocyte, neutrophil, and platelet counts; and urea nitrogen and creatinine concentrations. These parameters will be used to manage the side effects of lung cancer treatment in daily clinical practice.

Possible side effects in the TJ-43 group also include liver dysfunction, myopathy, hypersensitivity, and electrolyte abnormalities. The trial blood samples will be collected not only to examine safety (liver enzyme, creatinine phosphokinase, and electrolyte concentrations) but also to examine nutritional indices (total protein and albumin concentrations).

Japanese *Kampo* medicine is often used to manage the side effects of lung cancer treatment, although it is not necessarily used every time. Japanese *Kampo* medicine is prescribed on the unique basis of *Kampo* diagnosis, the concept of which differs from that of Western medicine. Because the concept of *Kampo* diagnosis has not yet been fully elucidated, it is necessary to explore the biomarkers reflecting the *Kampo* diagnosis and predicting the effect. Metabolomic analysis was recently utilized in clinical studies to explore biomarkers. Because metabolites are located downstream of deoxyribonucleic acid (DNA), ribonucleic acid (RNA), and proteins, metabolomics is closer to the phenotype than are other “omics.” Therefore, we will plan to explore various biomarkers to predict the effect and side effect of TJ-43 using plasma metabolomic analysis.

We will measure QOL using two self-administered QOL questionnaires (the QLQ-C30 and QLQ-LC13) at days 0, 7, and 22 or 29 (the start date of the next chemotherapy course).

### Data management

The investigators and clinical research coordinator will maintain individual records for each patient, such as the informed consent document, medical record, laboratory data, and Case Report Form, according to Good Clinical Practice. The investigators will record adverse effects in the patients’ Case Report Forms. Adverse events will be followed up continually until resolution. The investigators will be responsible for oversight of the data management of the trial. An independent Data Monitoring Committee will not be established. Instead, an independent medical advisor has been set up and will regularly assess safety, feasibility or any other problems. Data and all appropriate documentation will be stored for a minimum of 5 years after completion of the trial.

### Sample size

The sample size was calculated based on our retrospective data showing that the average dietary intake rate from day 1 to 5 was 72.2% ± 18.1% (mean ± standard deviation) in patients administered TJ-43 and 58.4% ± 18.2% in patients who were not administered TJ-43 (unpublished data). Based on this preliminary study, we calculated that 28 patients per group would be required to achieve a power of 80% with a two-sided significance level of *p* < 0.05 for detecting the superiority of concomitant treatment with TJ-43 by a *t* test. Here, the assumed effect size (*d*) was 0.76. To account for possible dropouts (10%), the target number of patients was, therefore, set at 30 per group (60 in total) (see Additional file 1).

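### The target of 30 per group covers about 7% dropout against the stated requirement of 28, not the 10% claimed; the cost in power is small

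*Protocol article*

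**What the plan says.** The Sample size section of the protocol article takes its inputs from the investigators' retrospective data on average dietary intake rate over days 1 to 5: "72.2% ± 18.1% (mean ± standard deviation) in patients administered TJ-43" and "58.4% ± 18.2% in patients who were not administered TJ-43". It says that "the assumed effect size (*d*) was 0.76".

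From these it concludes that "28 patients per group would be required to achieve a power of 80" per cent, "with a two-sided significance level of *p* < 0.05", "for detecting the superiority of concomitant treatment with TJ-43 by a *t* test". It then sets the recruitment target: "To account for possible dropouts (10%), the target number of patients was, therefore, set at 30 per group (60 in total". Additional file 1 is cited for the calculation and is not available here.

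The Randomization and blinding section gives the allocation as "in a 1:1 ratio using a block randomization method". Under Registration and Trial status, recruitment ends at 60 participants or in October 2017. The Study design and statistical analysis section analyses the primary endpoint by ANCOVA adjusted for baseline, in the full analysis set, and quotes n = 30 per group there.

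**The concern.** The article gives the requirement, the dropout allowance and the target in consecutive sentences and links them with a 'therefore'. A reader will conclude that 28 patients per group remain if 10% drop out. They do not: 10% of 30 is 3, and 27 remain.

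What is at stake is the accuracy of a stated design figure. Three losses per arm would look fully provided for and yet put the trial below its own declared requirement. The trial was still recruiting when the article was written, so the statement could be corrected before the results are read against it.

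**Working it through.** **Inputs** (Sample size section unless noted): means 72.2 and 58.4; SDs 18.1 and 18.2; d = 0.76; two-sided alpha 0.05; power 80%; t test; dropout 10%; target 30 per group; 1:1 allocation (Randomization and blinding).

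**1. Effect size.** Pooled SD = sqrt((18.1² + 18.2²)/2) = 18.15. Difference = 72.2 − 58.4 = 13.8. d = 13.8/18.15 = 0.760, which agrees with the article.

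**2. The stated 28.** Normal approximation: n = 2(1.960 + 0.842)²/0.76² = 27.18, rounded up to 28. The stated requirement is reproduced.

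**3. The dropout step.**
- Remaining after 10% loss from 30: 30 x 0.90 = 27, against 28 required.
- Loss that 30 can bear while keeping 28: (30 − 28)/30 = 6.7%, or 2 per arm.
- Target from n/(1 − dropout): 28/0.9 = 31.1, so 32 per group, 64 in total. Applied to the total of 56: 62.2, so 63.
- Target from the looser n x (1 + dropout): 28 x 1.1 = 30.8, so 31 per group, 62 in total.

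Neither formula, applied to the stated 28, gives 30. The shortfall against 60 is 2 to 4 patients.

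**4. Power at d = 0.76, two-sided 5%.** The noncentrality is d x sqrt(n/2). The exact t test has 2n − 2 degrees of freedom; the normal approximation is Φ(d x sqrt(n/2) − 1.960). For n = 27 the noncentrality is 0.76 x sqrt(13.5) = 2.792, and Φ(0.832) = 79.7%.

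| n per group | exact t | normal approximation |
|---|---|---|
| 27 (10% loss from 30) | 78.2% | 79.7% |
| 28 (stated requirement) | 79.75% | 81.2% |
| 29 | 81.2% | 82.5% |
| 30 (no loss) | 82.5% | 83.7% |

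At 27 per group, power is below 80% by 0.3 points (normal) or 1.8 points (exact). If dropout is random at 10% per patient rather than exactly 3 per arm, average exact power is 78.1%, so 27 is a fair stand-in.

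**5. Possible gain from ANCOVA.** The article gives no correlation between baseline and later intake, so this is an assumption. If the SD of 18.15 applies to the unadjusted outcome, adjustment multiplies it by sqrt(1 − r²). Exact-t power at 27 per group (ignoring the one degree of freedom spent on the covariate) is then 79.9% for r = 0.2, 81.9% for r = 0.3 and 88.6% for r = 0.5.

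**The case against.** **A common route does reach 30.** If the allowance is applied to the unrounded requirement, 27.18 x 1.1 = 29.9, which rounds up to 30. This may be what was done; Additional file 1 might show it. It explains the number but does not rescue the claim: a 10% loss from 30 still leaves 27, below both the stated 28 and the unrounded 27.18. It does mean that the size of the shortfall depends on when one rounds.

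**Dropout need not mean a missing primary endpoint.** Study treatment lasts 21 or 28 days, but the primary endpoint uses intake from day 0 to day 7 only, recorded meal by meal in hospitalised patients. Someone who leaves after day 7 still contributes to the full analysis set. This stands, and makes 27 evaluable per group a cautious figure. But the sample size paragraph itself treats dropouts as losses to be made up; if all were retained, no inflation would be needed.

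**ANCOVA may recover the power.** It may, at a modest correlation. But the article's claim is for a t test, and a possible gain elsewhere does not make the stated allowance correct.

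**Stronger readings that the document does not support.** A reader might infer that the design figures cannot be reconciled at all, or that the trial is materially underpowered. The rounding route above, a deficit of at most 1.8 points and the two possible offsets speak against both. A reader might also say that 28 is itself too few, because the exact t test needs 29 to pass 80%. But 79.75% is 80% to the nearest per cent, and 28 is what the normal approximation gives. Nor is 4 patients the shortfall as such; it is the upper end of a range set by convention.

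**Conclusion.** The point holds as a minor arithmetic error. Measured against the article's own requirement of 28 per group, 30 per group covers about 7% dropout (2 per arm), not 10%. With 10% loss, 27 remain, and the target is 2 to 4 patients short in total.

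The effect on power is 0.3 to 1.8 percentage points below 80%. This takes d = 0.76 as given, uses an unadjusted two-sided 5% t test, and assumes that every dropout loses the primary endpoint. Relaxing either of the last two could remove the deficit. The finding gives no reason to change the design, the analysis or the reading of the result.

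**What to change.** Keep 60 patients and restate the dropout sentence, for example: *30 per group allows for about 7% dropout (2 per group); with 10% dropout, 27 per group remain and power for the unadjusted t test is about 78% at d = 0.76.*

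If the allowance was applied to the unrounded 27.18, the text can say so, but it should still give the number remaining after 10% loss.

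The cost is one sentence and a slightly less favourable stated figure. Recruitment and analysis are unaffected.

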### Study design and statistical analysis

The effects of TJ-43 against chemotherapy-induced anorexia have yet to be determined. The RICH trial is designed to evaluate the efficacy of TJ-43 for anorexia in patients with lung cancer undergoing treatment with cisplatin-including chemotherapy. It is a placebo-controlled, double-blind, randomized trial that will be conducted at two institutions.

The primary endpoint will be the change in dietary intake from day 0 (the day before the start of chemotherapy) to day 7. The mean dietary intake in hospital (MDIH) is defined as the total hospital diet intake divided by the number of records. The investigators will calculate the MDIH each day from day 0 through day 7 for each patient, and the value at day 0 will be used as the baseline. The primary endpoint variable of this trial is the mean change in the MDIH from the baseline, averaged from day 1 through day 7. This will be evaluated by analysis of covariance (ANCOVA), which employs the baseline value as the covariate, to estimate the difference between the two treatment groups (*n* = 30 per group). Additionally, for ease of interpretation, the time profile of MDIH from day 1 through day 7 will be analyzed by a linear mixed-effects model using the baseline value as the covariate.

The secondary endpoints, namely the changes in nutritional indices (total protein and albumin concentrations), will also be analyzed by ANCOVA, which employs the baseline value (day 1) as the covariate. The changes in QOL assessment (QLQ-C30, QLQ-LC13) will be analyzed by ANCOVA for each item, which employs the baseline value (day 0) as the covariate. Items in the QOL assessment include the evaluation of nausea, vomiting, and anorexia. In addition, the proportion of patients who receive dose-reduced or delayed chemotherapy and the proportion of patients requiring extended hospitalization will be compared between the two treatment groups using the chi-square test or Fisher’s exact test. The incidence of adverse event will be compared by means of Fisher’s exact test.

The analyses of efficacy outcomes will be performed in the full analysis set. An interim analysis will not be performed.

This trial will be conducted in accordance with the World Medical Association Declaration of Helsinki. The protocol has been approved by the Institutional Review Board of each participating institute. Written informed consent will be obtained from all patients before enrollment and randomization by investigators. The SPIRIT Checklist is provided as an Additional file 2.

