### Registration

An eligibility report form will be sent to the Registration Center at Tsumura & Co. (Tokyo, Japan). Patients who meet all eligibility criteria will be randomly allocated to receive either TJ-43 (arm A) or placebo (arm B) at the individual institutions. Each participant must be hospitalized to receive chemotherapy. The placebo is indistinguishable from the TJ-43 in appearance. Investigators prescribing either TJ-43 or placebo to each patient will not know which patient is allocated to which arm.

Patients and investigators (including the investigators assessing blood tests) will be masked to the treatment assignment throughout the study. Each arm will comprise 30 patients. Recruitment began in November 2014 and will end in October 2017 or until 60 participants have been recruited.

This trial is being conducted at two institutions in Fukushima prefecture of Japan.

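### The primary ANCOVA and the mixed model name only baseline intake as covariate; adding institution costs almost nothing and gains power if site predicts change in intake beyond baseline

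*Protocol article*

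**What the plan says.** All references are to the protocol article.

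- **Model** (Study design and statistical analysis). The primary endpoint is compared by "analysis of covariance (ANCOVA), which employs the baseline value as the covariate, to estimate the difference between the two treatment groups". A linear mixed-effects model for the daily profile and the ANCOVAs for nutritional indices and quality of life are described in the same way, each with its own baseline value as covariate. Institution appears in none of them.
- **Outcome** (same section). "The primary endpoint variable of this trial is the mean change in the MDIH from the baseline, averaged from day 1 through day 7". The daily value is built as follows: "The mean dietary intake in hospital (MDIH) is defined as the total hospital diet intake divided by the number of records". Data collection adds: "For each meal, the weight of food (including tableware) before and after the meal will be measured".
- **Sites and allocation** (Registration). "This trial is being conducted at two institutions in Fukushima prefecture of Japan". Eligible patients are "randomly allocated to receive either TJ-43 (arm A) or placebo (arm B) at the individual institutions".
- **Method of allocation** (Randomization and blinding). Assignment is "in a 1:1 ratio using a block randomization method", from a list generated in advance. Stratification by institution is not mentioned.

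**The concern.** Food weight depends on what is served and how it is weighed, so institution is an obvious candidate predictor of this outcome. Two consequences are possible if it still predicts change in intake once the day 0 value is in the model.

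- The between-site variation stays in the residual, so the standard error of the treatment difference is larger than necessary.
- If the blocks run within institution, the design balances the arms by site but the analysis takes no credit for it. The test is then conservative and gives up power.

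What is at stake is efficiency in a trial of 60 patients. The validity of the comparison is not in question.

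**Working it through.** **Inputs.** From Sample size: means 72.2 and 58.4, standard deviations 18.1 and 18.2, *d* = 0.76, 28 per group, 80% power, two-sided 5%, *t* test. The share *s* of the variance left after baseline that institution explains is not in the documents. It is assumed and varied.

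**1. The plan's own figure.** Difference = 72.2 − 58.4 = 13.8. Pooled SD = √((18.1² + 18.2²)/2) = 18.15. *d* = 13.8/18.15 = 0.76. By the normal formula, *n* = 2 × (1.960 + 0.842)² × (18.15/13.8)² ≈ 27.2, which rounds up to 28. The stated 28 reproduces. The exact noncentral *t* at 28 per group gives 79.8%.

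**2. Power with and without institution.** The noncentrality is *d* × √(28/2) = 0.76 × 3.742 = 2.84. Baseline alone leaves 56 − 3 = 53 degrees of freedom and gives 79.7%. Adding institution leaves 52 and multiplies the residual SD by √(1 − *s*), so *d* becomes 0.76/√(1 − *s*):

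| Assumed *s* | SE ratio √(1 − *s*) | Power with institution | Gain (points) |
|---|---|---|---|
| 0% | 1.000 | 79.7% | 0.0 |
| 2% | 0.990 | 80.5% | 0.8 |
| 5% | 0.975 | 81.7% | 2.0 |
| 10% | 0.949 | 83.7% | 4.0 |
| 20% | 0.894 | 87.7% | 8.0 |

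**3. What these shares mean.** With two equal sites that differ by *D* within-site SDs after baseline, *s* = (*D*²/4)/(1 + *D*²/4). *D* = 0.3, 0.5, 0.8 and 1.0 give *s* = 2.2%, 5.9%, 13.8% and 20%. The gains are 0.8, 2.3, 5.5 and 8.0 points. With an 80:20 split of patients between sites, *D* = 0.5 gains 1.5 points.

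**4. How much survives baseline adjustment.** Suppose one site's meals are heavier by a constant *D* on every day. Assume equal sites, unit within-site SD at baseline and follow-up, and within-site correlation 0.5. Then:

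- total variance at each time = 1 + *D*²/4;
- covariance = 0.5 + *D*²/4;
- residual variance after baseline = (1 + *D*²/4) − (0.5 + *D*²/4)²/(1 + *D*²/4);
- residual variance within site = 1 − 0.5² = 0.75.

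For *D* = 1, the residual variance after baseline is 1.25 − 0.75²/1.25 = 0.80, so *s* = 1 − 0.75/0.80 = 6%. For *D* = 0.5 it is 0.765, so *s* = 1 − 0.75/0.765 ≈ 2%. A raw difference of 0.5 to 1 SD in meal weight therefore leaves only about 2% to 6%, worth roughly 1 to 2.5 points of power.

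**5. Type I error by simulation.** Setting: 56 patients, two equal sites, baseline slope 0.5, 5,000 runs per case, Monte Carlo standard error √(0.05 × 0.95/5,000) = 0.3 points. *D* is the site difference after baseline.

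| *D* | Baseline only, blocks within site | Baseline only, not stratified |
|---|---|---|
| 0.3 | 4.7% | 5.1% |
| 0.5 | 4.4% | 4.7% |
| 1.0 | 3.2% | 5.1% |

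There is no inflation. Only the 3.2% is clearly conservative; the 4.7% is within simulation error of 5%.

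**6. Cost when there is no site effect.** By the formula in step 2, power falls by 0.03 points. That formula treats the arms as balanced within site. In the simulation without stratification, chance imbalance raises the mean standard error from 0.2690 to 0.2716 (0.2716/0.2690 = 1.01, or 1%) when *D* = 0, and power goes from 79.1% to 78.2%. At *D* = 0.3 the term already breaks even (78.5% against 78.9%).

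**The case against.** The case for leaving the model alone has several parts.

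- *Differing diets are an inference.* A reader might take it that the two hospitals serve different meals. The article says only that there are two institutions and that food is weighed. This stands: the site effect is an assumption and may be nil.
- *Baseline already does most of the work.* The endpoint is change from the patient's own day 0 value, with that value as covariate. This stands in large part. Step 4 shows that a constant site difference is mostly, though not wholly, absorbed. A fall in grams proportional to portion size would not be a constant shift, but nothing in the article establishes one.
- *The planned power is not missed.* A reader might infer that the omission pushes the trial below 80%. It does not: that figure comes from an unadjusted *t* test that takes no credit for baseline or site. The table shows possible extra power.
- *No stated stratification factor is ignored.* A reader might take the words about allocation at the individual institutions to mean stratified blocks. They may equally say only where allocation happens. If the blocks are not stratified, chance imbalance between sites is not an error, since the standard error already reflects it.
- *A centre term may be in the full protocol or analysis plan.* That is possible, and its absence from those documents is not claimed. The article does, however, state the model and its covariate, so the stated choice can be commented on.
- *The weighed-food argument does not reach the secondary endpoints.* This stands. Laboratory values and questionnaire scores need a different reason, which only stratification would supply.

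**Conclusion.** The point holds as a conditional efficiency improvement. The stated models name baseline alone, in a two-site trial of weighed hospital food. Adding institution would shrink the standard error if site predicts change in intake beyond day 0. On the plan's own *d* = 0.76 and 28 per group, the gain runs from nothing to 8 points of power for assumed residual shares of 0% to 20%. About 1 to 2.5 points is more plausible, on the assumptions of equal sites, a constant site shift of 0.5 to 1 SD and a within-site correlation of 0.5.

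The documents do not support saying that power is lost as a matter of fact, that the stated 80% is missed for this reason, that a known stratification factor was dropped, or that the baseline-only analysis is invalid.

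**What to change.** Before unblinding, prespecify institution as a fixed effect next to the baseline value in the primary ANCOVA and in the mixed model. State whether the blocks are stratified by institution; if they are, carry institution into the secondary ANCOVAs as well.

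The cost is one model term and one degree of freedom (53 to 52 at 28 per group). If the blocks are not stratified and site has no effect, chance imbalance adds about 1% to the standard error. Trial status describes recruitment as ongoing, and Randomization and blinding places unblinding after the data are fixed, so the term can still be added without becoming a post hoc choice.
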